## Abstract

**Introduction:**

Self-management of hypertension, including self-monitoring and antihypertensive medication titration, lowers blood pressure (BP) at 1 year compared to usual care. The aim of the current trial is to assess the effectiveness of the Home and Online Management and Evaluation of Blood Pressure (HOME BP) intervention for the self-management of hypertension in primary care.

**Methods and analysis:**

The HOME BP trial will be a randomised controlled trial comparing BP self-management—consisting of the HOME BP online digital intervention with self-monitoring, lifestyle advice and antihypertensive drug titration—with usual care for people with uncontrolled essential hypertension. Eligible patients will be recruited from primary care and randomised to usual care or to self-management using HOME BP. The primary outcome will be the difference in mean systolic BP (mm Hg) at 12-month follow-up between the intervention and control groups adjusting for baseline BP and covariates. Secondary outcomes (also adjusted for baseline and covariates where appropriate) will be differences in mean BP at 6 months and diastolic BP at 12 months; patient enablement; quality of life, and economic analyses including all key resources associated with the intervention and related services, adopting a broad societal perspective to include NHS, social care and patient costs, considered within trial and modelled with a lifetime horizon. Medication beliefs, adherence and changes; self-efficacy; perceived side effects and lifestyle changes will be measured for process analyses. Qualitative analyses will explore patient and healthcare professional experiences of HOME BP to gain insights into the factors affecting acceptability, feasibility and adherence.

**Ethics and dissemination:**

This study has received NHS ethical approval (REC reference 15/SC/0082). The findings from HOME BP will be disseminated widely through peer-reviewed publications, scientific conferences and workshops. If successful, HOME BP will be directly applicable to UK primary care management of hypertension.

**Trial registration number:**

ISRCTN13790648; pre-results.

Strengths and limitations of this studyThe study develops existing efficacious antihypertensive titration procedures into an online format.Home and Online Management and Evaluation of Blood Pressure (HOME BP) combines medication intensification with lifestyle change and behavioural support.The study has been designed to facilitate implementation within a primary care context.

## Introduction

Blood pressure (BP) is a key risk factor for cardiovascular disease, the largest cause of morbidity and mortality worldwide.^1^ The health survey for England (2012) identified that ∼31% of men and 27% of women in England have hypertension,^2^ yet over one-third of all treated patients currently fail to reach national guidelines for BP control.^3^ The mean BP in the UK currently ranks among the highest in Europe (27th/35), and the benefits of a population-wide reduction to levels seen in countries such as Denmark and Spain (which are among the lowest) would mean a 10 mm Hg systolic blood pressure (SBP) reduction.^4^ A 10 mm Hg reduction in BP is estimated to lead to a 41% reduction in stroke and a 22% reduction in coronary heart disease (CHD).^5^ New strokes affect over 120 000 patients per annum in the UK, and stroke is the third leading cause of death and the most important cause of adult disability, representing 4.4% of direct National Health Service (NHS) costs (notwithstanding costs to social services, patients and carers).

Factors responsible for suboptimal BP control include those due to patients, physicians and the health system.^6^ The key patient factors are adherence to medication and other health behaviours.^7^
^8^ Clinical inertia is another key issue, whereby clinicians fail to intensify treatment, despite evidence of inadequate control. It is estimated that clinical inertia may account for almost 20% of the variance in BP control,^9^ with evidence suggesting that treatment intensification fails to occur in nearly half (45%) of consultations in which patients had a single BP reading above target, and around a third (36%) with two successive readings above target.^10^ Lack of intensification may be due, in part, to the ‘white-coat effect’, where BP readings in clinic consultations are elevated in comparison to self-monitored home BP readings;^11^
^12^ awareness that clinic readings may be inaccurate may contribute to clinician and patient reluctance to implement medication changes. Even with self-monitoring of BP, clinical inertia can be profound.^13^

There is evidence that self-monitoring BP at home is useful in improving medication adherence, reducing therapeutic inertia and controlling BP,^12^
^14–17^ and research by our team and others has shown that sustained reductions in BP can indeed be achieved by linking self-monitoring to preplanned medication titration when hypertension is uncontrolled.^17–21^ It can also detect and treat masked uncontrolled hypertension.^22^ While some evidence suggests that aggressive titration of antihypertensive medication without behavioural support is optimal for controlling BP,^23^ further evidence suggests that greater reductions in BP may be achieved by the addition of behavioural support for self-monitoring.^19^
^24^
^25^ This may be further facilitated when combined with efficacious lifestyle changes, such as weight reduction, sodium restriction and increasing physical activity,^26^
^27^ therefore HOME BP will combine all of these components.

### Rationale and risk-benefits for the current trial

Increasingly widespread access to the internet and mobile phones^28^
^29^ means that healthcare digital interventions (DIs) (also known as online interventions or computer-based health interventions within the literature) are accessible to the majority of patients and can be used to provide information and support at any time the patient needs it.^30^ DIs can empower patients by providing better access to personalised information and support for active involvement in treatment and self-management.^30^ A large meta-analysis found a small but significant positive effect of DIs on health-related behaviours,^31^ while a Cochrane review found evidence that computer-based health interventions for those with chronic health conditions significantly improved knowledge, health behaviours and clinical outcomes.^32^ DIs have the potential to make significant savings by automating routine aspects of patient education, monitoring and support, freeing up health professional resources for when patients most need them.^33^ There is accumulating evidence that DIs can deliver better and more efficient healthcare in the context of hypertension,^34^
^35^ confirmed by a recent systematic review and meta-analysis undertaken by our team.^36^ Therefore, the HOME BP programme has been developed to incorporate previously identified effective intervention components (self-monitoring, preplanned medication titrations and behavioural support) delivered in an acceptable and feasible online format.

### Study aims and research questions

The primary aim of the HOME BP trial is to assess the feasibility, acceptability, effectiveness and cost-effectiveness of adding the HOME BP intervention (comprising the HOME BP online DI, self-monitoring, medication titration and lifestyle interventions with nurse support) into primary care for the self-management of hypertension in comparison to usual care.

Main research question:
Does the HOME BP intervention to assist self-monitoring and self-management of uncontrolled hypertension result in greater control of SBP after 1 year?

Secondary research questions:
Does the HOME BP intervention to assist self-monitoring and self-management of uncontrolled hypertension result in greater control of SBP and diastolic blood pressure (DBP) after 6 months and DBP after 1 year?Is the HOME BP intervention more cost-effective than usual care in managing poorly controlled hypertension in primary care?

Process analysis research questions:
Which factors are related to patient engagement and adherence to HOME BP?Which factors are related to patient medication adherence and uptake of recommended medication titrations?Does the inclusion of lifestyle change choices and behavioural support result in engagement with lifestyle change?Is the HOME BP intervention acceptable to patients when integrated into routine practice?What are patient and healthcare practitioner views and experiences of the HOME BP intervention and its addition into primary care for the self-management of poorly controlled hypertension?

## Methods and analysis

### Study design and setting

The HOME BP intervention for the self-management of high BP consists of the integrated patient and healthcare practitioner HOME BP online DI, BP self-monitoring, health professional directed and supervised titration of antihypertensive medication and user-selected lifestyle modifications, for people with uncontrolled essential hypertension. The HOME BP study is a pragmatic, randomised controlled trial comparing the HOME BP intervention with optional nurse support to a control group receiving usual hypertension care within a UK primary care setting.

### Study participants

#### Identification, follow-up and non-participation

Eligible participants will be identified from electronic database searches of clinical systems of collaborating general practices. Records of potentially eligible patients will be further screened by general practitioners (GPs) to remove participants known to meet exclusion criteria. Remaining potentially eligible patients will be invited by letter from the practice to attend a baseline clinic to establish eligibility, take consent, collect baseline data and randomise consented patients. Individuals not wanting to take part will be provided with a form to return should they wish to decline to take part in the trial. This will ask for basic demographic information and their reasons for declining, including an option not to give a reason if they prefer not to. The practice nurse (or other practice member as delegated by the lead GP) will have the option to follow-up invited patients by telephone after 1 month without response. All patient identification prior to consent will be conducted independently of the research team to maintain confidentiality.

#### Eligibility criteria

Eligibility criteria will aim to capture adult patients with treated but uncontrolled hypertension managed in primary care who will be aged 18 or over, have a Read code for hypertension in the clinical record (confirming hypertension), a current prescription of antihypertensive medication and a mean BP reading (calculated from the second and third BP readings) of >140/90 mm Hg taken during a baseline clinic appointment. Eligible patients will also be required to have access to the internet and be able to comprehend the website.

#### Exclusion criteria

Exclusion criteria will include an inability to self-monitor (eg, diagnosis of dementia), a mean baseline BP reading of >180/110 mm Hg (stage 3 hypertension requiring more urgent intervention than would be available in the trial), hypertension not managed by family doctor (the trial facilitates primary care titration of medication), prescribed more than three antihypertensive medications (ie, resistant hypertension), chronic kidney disease (CKD) stage 4–5 or CKD stage 3 not managed by the GP (likely to be under specialist care and requiring different BP targets), terminal disease or other condition which in the opinion of the family doctor makes them inappropriate to take part, pregnant or breast feeding, a history of proteinuria (albumin creatinine Ratio (ACR) >30 mg/mmol) (different BP targets), postural hypotension (>20 mm Hg systolic drop after 1 min standing) (for whom intensification of BP medication may be inappropriate), atrial fibrillation (self-monitoring with oscillometric equipment not suitable), an acute cardiovascular event in the previous 3 months (BP and antihypertensive medication may not be stable) or a household member already enrolled on the study (to avoid bias). Participants who are involved in any other BP research will not be able to take part in the study.

#### Randomisation

Participants will be randomised in a 1:1 ratio to receive either usual care or the HOME BP intervention with optional nurse support using the HOME BP online system. Minimisation will be used taking into account participants' baseline SBP, age, diabetes status and practice. Patients are randomised to the optimal group 80% of the time. Any random numbers the minimisation routine might need will be computer generated, therefore bypassing study team involvement.

#### Participant flow through the study

At baseline, all patients will receive a consultation where informed consent will be taken, as well as clinical measures (confirmation of raised BP, height, weight) and medical history. Hypoglycaemic episodes in the last 6 months will be recorded for diabetic patients. BP will be measured after 5 min rest with a validated electronic automated sphygmomanometer (BP TRU BPM 200). Participants will be seated, and BP will be measured in their left arm unless there is a reason not to (principally lymphoedema or other medical condition). Six BP readings will be taken at intervals of 1 min, with the mean of the second and third readings used for the primary outcome. Patients will complete demographic measures and baseline assessments at home via HOME BP online, following which automatic allocation to intervention or usual care group will be triggered. Patients will be immediately notified of their allocation through HOME BP online, confirmed by email or letter. Practice staff will also be notified of patient group allocation by email. Participants will be informed that the research team will have access to their personal and study data to stay in touch with them throughout the study.

Following randomisation, all patients will receive a BP medication review with a trained HOME BP prescriber (one or more GPs or nurse prescriber's nominated by the practice). For patients allocated to the intervention group, prescribers will be asked to select and agree an individualised medication titration plan (including three potential medication changes should BP remain above target). Participants allocated to usual care will receive a routine hypertension medication review. None of the study participants (patients or healthcare practitioners) will be blinded to group allocation. At 6-months and 12 months after randomisation, all patients will be invited to a follow-up appointment with an independent research nurse. This may take place within the clinic or at a participant's home. Patients will be asked to not reveal their group allocation at this appointment, as research nurses completing the 6-month and 12-month follow-up appointments will be blinded to the patient’s group. All follow-up BP measurements will be recorded no earlier than 2 weeks before the follow-up date, and no later than 4 weeks following the follow-up date at the 6-month follow-up. The follow-up period will be extended up to a maximum of 8 weeks for the 12-month follow-up. Patient BP readings and clinical measures will be taken in the same way as baseline and follow-up questionnaires completed through HOME BP online. Participant flow through the trial is outlined in figure 1. Participants will be withdrawn from the study if they become no longer eligible to participate (eg, due to pregnancy). Participants who choose not to continue with the study will be offered the opportunity to continue self-monitoring only rather than withdrawing completely from the study, and asked if they would be prepared to attend follow-up appointments.

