### Statistical analysis

The principal analysis will use raw and adjusted data and will be performed at the end of the trial after all data have been collected. The primary analysis will use general linear modelling to compare intervention and usual care SBP at follow-up adjusting for baseline BP, practice (as a random effect), BP target levels and gender. Analyses will be on an intention to treat basis with imputation. Secondary analyses will be reported for complete cases. No interim analyses will be performed. A sensitivity analysis will examine the potential effect of missing data using multiple imputation. Planned subgroup analyses will be of BP target groups, older versus younger (65 as threshold), men versus women and better controlled at baseline versus worse controlled at baseline (median SBP). Secondary analyses will use similar techniques to assess differences between groups in SBP at 6 months, DBP at 6 months and 12 months, medication use and quality of life. Additional analyses will examine patient and healthcare professional adherence to advice and study processes, website usage and support provision. Process analyses will be reported elsewhere, but will assess the impact of patient enablement and self-efficacy, symptom perceptions and medication beliefs on outcomes. These analyses will also examine the relationship between support uptake, engagement with healthy behaviour change and outcomes.

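### The rule that withdraws randomised participants from the study once they lose eligibility creates avoidable missing outcomes and undermines the intention-to-treat analysis

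*Protocol article*

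**What the plan says.** Under Participant flow through the study, the protocol article says: "Participants will be withdrawn from the study if they become no longer eligible to participate (eg, due to pregnancy". The sentence after it deals with people who decide for themselves to stop. They are offered self-monitoring alone as an alternative to leaving altogether, and are "asked if they would be prepared to attend follow-up appointments". No matching request is written for people whom the trial withdraws.

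The article does not say which eligibility criteria continue to apply after randomisation. Some of the Exclusion criteria carry no tie to baseline, among them "prescribed more than three antihypertensive medications (ie, resistant hypertension" and "postural hypotension (>20 mm Hg systolic drop after 1 min standing", a recent acute cardiovascular event, and any condition that the family doctor considers to make the person unsuitable. Patients and practitioners know the allocation. Only the intervention arm has an agreed titration plan, "including three potential medication changes should BP remain above target".

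Under Statistical analysis: "Analyses will be on an intention to treat basis with imputation". Two further sentences follow: "Secondary analyses will be reported for complete cases" and "A sensitivity analysis will examine the potential effect of missing data using multiple imputation".

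**The concern.** Intention to treat needs outcomes to be sought from everyone randomised, whatever happens to them later. A rule that removes people from the study on post-randomisation grounds works against that. If those grounds are related to blood pressure, to its treatment or to harm, the missing outcomes are informative. If they arise more often in one arm, the comparison between arms can shift.

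The article already separates stopping the intervention from leaving the study, but it applies that separation only to voluntary stoppers. A participant withdrawn for loss of eligibility has no written route to the 6- and 12-month visits. The 12-month systolic pressure is the primary outcome, and an outcome that was never collected cannot be recovered at the analysis stage. Imputation keeps such a person in the analysis set, but the imputed value rests on an assumption about the missing reading. A complete-case analysis loses the person.

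**Working it through.** **1. The plan's own figure.** Inputs from Sample size consideration: difference 5 mm Hg, SD 17 mm Hg, power 90%, 244 per group, 15% dropout, 287 per group. The significance level is not stated there; two-sided 5% is assumed.

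- n per group = 2 × (1.9600 + 1.2816)² × 17² / 5² = 242.9, so 243. The stated 244 reproduces, with power 90.1%.
- 287 × 0.85 = 243.95, so the dropout allowance also reproduces.

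No stated figure needs correcting. The total of 574 stands if the people concerned are still followed up.

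**2. Which criteria could the rule reach?**

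| Criterion | Tied to baseline in the text? | Can change after randomisation? |
|---|---|---|
| Raised BP for entry (>140/90) | Yes, baseline clinic | Not a trigger on the wording |
| BP >180/110 | Yes, baseline reading | Not a trigger; Medication titration procedures handle later high readings without withdrawal |
| More than three antihypertensives | No | Yes |
| Postural hypotension | No | Yes |
| Acute cardiovascular event | No | Yes |
| Family doctor's opinion of suitability | No | Yes, and given with knowledge of allocation |
| Pregnancy | No | Yes; the only trigger named, and not caused by allocation |

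The rule could therefore reach several criteria that treatment or disease can alter. The article does not say that it does.

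**3. Possible shift in the treatment contrast.** Let w be the excess fraction of one arm that is withdrawn, and D the difference in mean 12-month systolic pressure between those withdrawn and those retained. The full-arm mean is (1 − w) × R + w × (R + D) = R + w × D, where R is the mean of those retained. If nothing is recovered by imputation or baseline adjustment, the arm mean, and so the contrast, is off by w × D. Both w and D are assumptions.

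| w | D = 5 | D = 10 | D = 17 |
|---|---|---|---|
| 2% | 0.10 | 0.20 | 0.34 |
| 5% | 0.25 | 0.50 | 0.85 |
| 10% | 0.50 | 1.00 | 1.70 |

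The values are in mm Hg. Against the 5 mm Hg target they run from 0.1/5 = 2% to 1.7/5 = 34%. If the intervention arm loses people with high pressure, the shift favours the intervention; if it loses people with low pressure, as postural hypotension might imply, the shift goes the other way.

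**4. Scale against sampling error.** SE = 17 × √(2/244) = 1.54 mm Hg. With no true effect, a shift b gives a two-sided error rate of P(|Z + b/SE| > 1.96): 6.2% for b = 0.5 and 10.0% for b = 1.0.

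**5. Precision.** If the rule removed extra people equally from both arms, beyond the 15% allowance, 287 × (1 − 0.15 − w) per group would remain: 238 for w = 2% (power 89.4%), 230 for 5% (88.3%) and 215 for 10% (86.2%). The loss of power is modest; possible bias matters more.

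**The case against.** The strongest reply is that the sentence is loose rather than harmful. Its only example is pregnancy, which allocation does not cause. It cannot mean that every criterion is re-applied throughout, or controlled blood pressure itself would become a reason for removal. The section on titration contains no withdrawal step. The planned steps are called changes, so they need not add drugs, and the number of drugs is itself a process measure. The same section on participant flow invites all patients to both follow-up visits, and practitioners report all adverse events throughout the trial. Finally, a journal article condenses a fuller protocol.

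Much of this stands, and it limits the point. A reader might infer that the rule is a treatment-driven exclusion: intervention patients reach a fourth drug and are removed for it. The documents do not say so; that trigger is an inference from an unrestricted sentence. A reader might also add later readings above 180/110 to the list, but that criterion is worded as a baseline reading.

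What does not stand is the suggestion that nothing needs changing. The withdrawal sentence is mandatory, refers to the study and is open-ended. It comes after the general invitation and is more specific. The retention request that follows covers only those who choose to stop. This is a stated rule, not a detail left to another document.

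**Conclusion.** The point holds in limited form. Followed as written, the rule produces missing outcomes that the trial could avoid and that may be informative, so it undermines the intention-to-treat analysis.

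It would go too far to say that it contradicts that analysis. Nothing in the article removes withdrawn people from the analysis set or discards data already collected, and imputation can keep them in. The weakness is that the imputed values depend on assumptions about readings that need not have been lost. Standard multiple imputation assumes that the readings are missing at random.

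The size is not known. The range of about 0.1-1.7 mm Hg rests entirely on assumed excess withdrawal of 2-10% in one arm and an assumed pressure difference of 5-17 mm Hg, with nothing recovered by imputation or baseline adjustment. The documents give no rate, no difference and no direction. If withdrawals turn out to be few and mostly for pregnancy, the effect would be small. This is a worthwhile and cheap correction rather than a fault that by itself puts the primary result in doubt.

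**What to change.** Replace the withdrawal sentence with a statement that:

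- eligibility is assessed up to randomisation;
- a participant who later meets an exclusion criterion is recorded, where applicable, as having discontinued the intervention, not as having left the study;
- that participant is still invited to the 6- and 12-month visits and included in the notes review, unless consent for follow-up is withdrawn;
- that participant is analysed in the group to which they were randomised.

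Whether the intervention continues for such a person remains a clinical decision, and the amendment need not touch it.

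The cost is a short amendment and a matching line in the instructions to practices and research nurses. The visits and the notes review are already planned for both groups, and the sample size does not change. It should be done before follow-up begins, because readings that were not taken cannot be obtained later.
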